#### 12.4.3 ANALYSIS OF THE SECONDARY ENDPOINT(S)

- **Outcomes:** Frailty progression, ADL/IADL scores, healthcare utilization, costs, patient satisfaction, medication adherence, mortality, along with all the laboratory measurements.
- **Method:** Each secondary outcome will be clearly defined and analyzed to evaluate the broader impacts of the intervention on participants' health and well-being. Frailty progression will be assessed through a frailty score as a continuous measure. Functional limitations will include work-limiting conditions, mobility, Activities of Daily Living (ADL), and Instrumental Activities of Daily Living (IADL), scored on an ordinal scale, using categorical measures (e.g., "able" vs. "unable"). Health care utilization will be measured by tracking healthcare events (e.g., visits, hospitalizations) in a binary or categorical format, while health care expenditure will be recorded as a continuous variable, capturing both mean and median expenditures. Medical adherence will be represented as a percentage, indicating the proportion of prescribed medications participants adhered to. Statistical comparisons of these secondary outcomes between the intervention and control groups will employ appropriate tests for each outcome variable type to assess differences. Mixed-effect models will calculate adjusted odds ratios to determine effect sizes, with corresponding confidence intervals to quantify the intervention's impact.

---

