### 3 OBJECTIVES AND ENDPOINTS

The primary healthcare intervention package (Multi-FrAME) is expected to improve health outcomes for older adults with multimorbidity and frailty, including a reduction in frailty progression and enhanced functional ability. This will assess the following outcomes.

| Objectives                                                                                      | Endpoints                                                   | Justification For Endpoints                                                       | Putative Mechanisms Of Action                                   |
|-------------------------------------------------------------------------------------------------|-------------------------------------------------------------|-----------------------------------------------------------------------------------|-----------------------------------------------------------------|
| 3.1 PRIMARY OBJECTIVES                                                                          |                                                             |                                                                                   |                                                                 |
| Assess the effectiveness of the Multi-FrAME package in improving health-related quality of life | Change in EQ-5D-5L index scores at 0, 6, and 12 months      | EQ-5D-5L is validated for use in India and measures multiple dimensions of health | Comprehensive care improves physical, mental, and social health |
| 3.2 SECONDARY OBJECTIVES                                                                        |                                                             |                                                                                   |                                                                 |
| Evaluate improvement in frailty                                                                 | Change in frailty index scores (deficit accumulation model) | Reliable measure for frailty changes                                              | Nutritional support and physical activity reduce frailty        |
| Assess improvement in ADL/IADL                                                                  | Change in ADL/IADL scores using Lawton IADL Scale           | Validated measure for functional status                                           | Improved physical and cognitive functioning                     |

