**B. Secondary Endpoints:**

i. **Frailty Index:**

- a. **Tool:** Cumulative Deficit Frailty Index (Rockwood et al., 2005)
- b. **Details of the index:** The study will employ a deficit-based frailty index (FI) to assess frailty status, following the cumulative deficit model (Ghosh et al., 2023). The FI will be constructed using 40 health-related variables covering multiple domains, including chronic diseases, functional limitations, cognitive impairments, and self-perceived health status. Each variable will be coded as 0 (deficit absent), 1 (deficit present), or assigned an intermediate value (e.g., 0.5) for partial deficits. The FI score for each participant will be calculated by dividing the total number of deficits present by the total number of variables assessed, resulting in a score ranging from 0 to 1. Based on this score, participants will be categorized as robust ( $FI \leq 0.15$ ), prefrail ( $FI > 0.15$  to  $\leq 0.24$ ), or frail ( $FI > 0.25$ ). This method provides a comprehensive and standardized approach to measuring frailty by accounting for the accumulation of health deficits across multiple domains.
- c. **Assessment Schedule:** Assessed at baseline, 6, and 12 months.

ii. **ADL/IADL:**

- a. **Tool:** Lawton and Brody Instrumental Activities of Daily Living Scale (Lawton & Brody, 1969)
- b. **Assessment Schedule:** Conducted at baseline, 6, and 12 months.

iii. **Healthcare Utilization:**

- a. **Tool:** Custom questionnaire capturing healthcare visits and hospital admissions.
  - b. **Data Collection:** Monthly via participant health diaries and healthcare records.
- iv. **Healthcare Expenditure:**
  - a. **Assessment:** Monthly data collection from participant reports and receipt submissions.
- v. **Medication Adherence:**
  - a. **Tool:** Medication Adherence Reporting Scale (MARS) (Thompson et al., 2000)
  - b. **Frequency:** Assessed at 0, 6, and 12 months.
- vi. **Patient Satisfaction:**
  - a. **Tool:** Patient Satisfaction Questionnaire (Greenfield & Attkisson, 1989)
  - b. **Frequency:** Evaluated at 6, and 12 months.
- vii. **Mortality Rates:**
  - a. **Data Collection:** Continuous monitoring throughout the study period using health records and family reports.

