## 15 ABBREVIATIONS AND SPECIAL TERMS

- **PHC:** Primary Healthcare Centre
- **EQ-5D-5L:** EuroQol 5-Dimensions, 5 Levels
- **MAQ-PC:** Multi-Condition Assessment Questionnaire for Primary Care
- **DART:** Dementia Assessment Rapid Test
- **ICMR:** Indian Council of Medical Research
- **RMRC:** Regional Medical Research Centre
- **HWC:** Health and Wellness Centre
- **EDC:** Electronic Data Capture

- **DBMS:** Database Management System
- **PI:** Principal Investigator
- **DMC:** Data Monitoring Committee
- **SOPs:** Standard Operating Procedures
- **ICT:** Information and Communication Technology
- **QA/QC:** Quality Assurance/Quality Control
- **ICC:** Intraclass Correlation Coefficient
- **SAE:** Serious Adverse Event
- **AE:** Adverse Event
- **PROMs:** Patient-Reported Outcome Measures
- **ADL/IADL:** Activities of Daily Living/Instrumental Activities of Daily Living
- Protocol Amendment History- NA

List of CRFS for the trial

| CRF                      | Purpose                                       | Time Point    | Key Constructs/Variables                                                                              |
|--------------------------|-----------------------------------------------|---------------|-------------------------------------------------------------------------------------------------------|
| Eligibility CRF          | Assess participant eligibility                | Screening     | Inclusion/exclusion criteria, consent status                                                          |
| Recruitment/Baseline CRF | Collect initial participant data              | Baseline      | Demographics, baseline health status, medical history                                                 |
| Follow-up CRF            | Track ongoing participant status and outcomes | 6, 12, months | Health-related quality of life, frailty index, ADL/IADL, medication adherence, healthcare utilization |

[figure not shown]

|                                            |                                               |              |                                                                |
|--------------------------------------------|-----------------------------------------------|--------------|----------------------------------------------------------------|
| Exit CRF                     | Record reasons for study exit                 | Upon exit    | Mortality, migration, withdrawal of consent, ineligibility     |

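### The ADL/IADL endpoint is a change in score on an instrumental-ADL scale, but section 12.4.3 widens it to constructs with no named instrument and reports it as odds ratios

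*Protocol*

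**What the plan says.** The objectives table (section 3.2) gives the endpoint as "Change in ADL/IADL scores using Lawton IADL Scale". Section 9.1, part B, lists a single tool under the ADL/IADL heading, the "Lawton and Brody Instrumental Activities of Daily Living Scale", assessed at baseline, 6 and 12 months. Section 15 expands the label as "Activities of Daily Living/Instrumental Activities of Daily Living", that is, as two constructs.

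Section 12.4.3 opens with an outcome list that keeps the scores: "Frailty progression, ADL/IADL scores, healthcare utilization, costs, patient satisfaction, medication adherence, mortality, along with all the laboratory measurements". Its method text then describes a wider outcome: "Functional limitations will include work-limiting conditions, mobility, Activities of Daily Living (ADL), and Instrumental Activities of Daily Living (IADL"). The coding is given as "scored on an ordinal scale, using categorical measures (e.g., 'able' vs. 'unable"). For effect size, the section says: "Mixed-effect models will calculate adjusted odds ratios to determine effect sizes".

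**The concern.** Three things should agree for any endpoint: what is measured, what is analysed and how the effect is expressed. Here they do not.

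The measurement sections supply a scale that, by its own title, covers instrumental activities. The analysis section adds basic ADL, mobility and work-limiting conditions. It then moves from a change in score to categories and odds ratios.

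Two consequences follow. A result on the Lawton scale could be reported under the ADL/IADL label as an effect on basic ADL, which that scale is not named as measuring. And because the variable, its coding and its effect measure are not tied together, an analyst could choose among several functional variables, or choose an able/unable cut, after seeing the data. Section 12.4.3 itself promises a clear definition of each secondary outcome.

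**Working it through.** The protocol states no effect size, SD, event rate or sample size for function, so there is no figure to reproduce. The main check compares the text.

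**Step 1: construct and instrument.**

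| Construct in 12.4.3 | Instrument linked to this endpoint in 3.2 or 9.1 |
|---|---|
| IADL | Lawton scale |
| Basic ADL | none |
| Mobility | none; elsewhere only an EQ-5D-5L domain (12.4.2) |
| Work-limiting conditions | none |

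The frailty index in 9.1 has 40 variables, with functional limitations among its domains. No items are listed and the index is not linked to this endpoint. The list of case report forms in section 15 repeats ADL/IADL for the follow-up form without naming a tool.

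**Step 2: scale and effect measure.**

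| Place | Scale |
|---|---|
| 3.2 | change in score |
| 12.4.3, outcome list | scores |
| 12.4.3, method | ordinal and categorical, able/unable as an example |
| 12.4.3, effect size | adjusted odds ratio |

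The natural summary of a change in score is a difference in means. An odds ratio fits a binary outcome or an ordinal (cumulative-odds) model. The text does not say which of these is meant.

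**Step 3: what dichotomising would cost, as an illustration only.** Assume a normal score, a small effect and a share p classed as unable. For independent data, the efficiency of the split relative to the score is φ(z_p)²/[p(1−p)]:
- p = 0.5: 0.637
- p = 0.2: 0.490
- p = 0.1: 0.342

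At a median split the loss is 1 − 0.637 = 0.363, about 36%.

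This is a cluster trial, and splitting the score also lowers the ICC. Section 12.2 plans with an ICC of 0.24; assume it also holds for the underlying functional score. At a median split the binary ICC is (2/π)·arcsin(0.24) = 0.154. With m participants per cluster, the retained efficiency is

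0.637 × [1 + (m−1)·0.24] / [1 + (m−1)·0.154].

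The protocol gives no m, so take 20 to 100:
- m = 20: 0.637 × 5.56 / 3.93 = 0.90
- m = 100: 0.637 × 24.76 / 16.28 = 0.97

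The loss at a median split is then about 3–10%. More uneven splits cost more under the same assumptions. At 20/80 the binary ICC is 0.128, and retained efficiency is 0.79 (m = 20) to 0.89 (m = 100). At 10/90 the binary ICC is 0.099, and it is 0.66 to 0.79.

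**The case against.** A reader might infer that the protocol throws away the Lawton score and analyses function as able versus unable. The documents do not support that. Able/unable is only an example, the same sentence calls the scale ordinal, and the outcome list still names scores. The example could also describe how single items are coded before they are summed. Odds ratios do not imply dichotomising either, since an ordinal mixed model also produces them. This part of the objection stands: the text permits a split but does not prescribe one.

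A reader might also infer that dichotomising would cost 36–66% of the sample. Those figures come from the independent-data formula. Strong clustering shrinks the loss, as the third step of the working shows.

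It can further be said that model choice and score coding are commonly left to a statistical analysis plan, and that the case report forms and the manual of operating procedures are annexures not shown and may contain an ADL form. Both are fair, but neither resolves the point. The protocol's own sections describe different constructs and different scales for one endpoint, and a form in an annexure would not reconcile them.

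Finally, the odds-ratio sentence in 12.4.3 covers all secondary outcomes. That part of the mismatch is therefore not peculiar to function; the widening of the construct is.

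**Conclusion.** The inconsistency holds. Sections 3.2 and 9.1 define a change in score on an instrumental-ADL scale. Section 12.4.3 extends this to basic ADL, mobility and work limitation with no linked instrument, and describes categorical measures and odds ratios that do not match the stated endpoint. This rests on the text alone and needs no assumption.

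It concerns one secondary endpoint and does not touch the primary analysis. It should be corrected because the functional claim depends on it and the correction is cheap.

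The cost of dichotomising is conditional on a split being made: about 36% at a median split for independent data, or about 3–10% with an ICC of 0.24 and clusters of 20–100. That ICC is the planning value in section 12.2, and neither it nor the cluster size is documented for this endpoint. The figures are an illustration and do not show an error in any stated number.

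**What to change.** - **Name the endpoint as measured.** Use IADL (Lawton total score) wherever the label appears as this outcome: sections 1.1, 1.2, 1.3, 3.2, 9.1 and 12.4.3. Alternatively, if a basic-ADL instrument is already on the case report forms, name it in 3.2 and 9.1 and keep basic ADL as its own outcome.
- **Settle the added constructs.** Delete mobility and work limitation from 12.4.3, or mark them exploratory if they are already collected. Do not assume that frailty-index items can supply them, because the protocol does not list those items.
- **Fix one scale and one effect measure.** Analyse the Lawton score in a mixed model with a cluster effect, adjusted for its baseline value. Report a mean difference, or a cumulative odds ratio if the score is treated as ordinal. Keep able/unable descriptive only.

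The cost is a wording amendment, with no new data collection. The downside is a narrower functional claim if basic ADL is dropped.

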| Decrease healthcare utilization                                                                 | Reduction in healthcare visits and hospital admissions      | Reflects stabilized health conditions                                             | Coordinated care reduces the need for acute services            |
| Decrease healthcare expenditure                                                                 | Reduction in total healthcare costs                         | Economic impact of reduced healthcare spending                                    | Efficient management techniques                                 |

|                               |                                                                |                                            |                                                      |
|-------------------------------|----------------------------------------------------------------|--------------------------------------------|------------------------------------------------------|
| Improve medication adherence  | Increase in Medication Adherence Reporting Scale (MARS) scores | Indicates adherence behavior changes       | Education and psychosocial support improve adherence |
| Increase patient satisfaction | Higher scores in Patient Satisfaction Questionnaires           | Direct feedback on care experience         | Patient-centered care enhances satisfaction          |
| Reduce mortality rates        | Reduction in all-cause mortality over study duration           | Key determinant of long-term effectiveness | Comprehensive care strategies prolong life           |

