## 5 STUDY POPULATION:

### 5.1 INCLUSION CRITERIA

- Adults aged 60 years and above.
- Patients with multimorbidity, defined by two or more chronic health conditions, as assessed by the MAQ-PC plus tool(Pati et al., 2016).
- Frailty index score of  $\geq 0.25$  (Ghosh et al., 2023).
- Residents of Bhubaneswar city.

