## 6.2 ADMINISTRATION AND/OR DOSING

- **Intervention Delivery:** Conducted by trained healthcare professionals at participating PHCs, assisted by trained investigators from the study team.
- **Monthly Contact Sessions:** All testing, data collection, clinical management, physiotherapy, and physical activity reviews conducted during these sessions.
- **Health Diary:** Each participant will receive a "Health Diary," serving multiple purposes:
  - **Intervention Log:** Enables participants and caregivers to maintain a daily record, helping verify intervention fidelity.
  - **Documentation Hub:** A single point for filing lab reports and documenting other medications and health updates during the trial.
  - **Information, Education, and Communication (IEC):** Contains materials for health promotion, behavior change, and education. Participants can refer to these resources for ongoing learning and support.

| Intervention Category               | Specifications                                                                                                                                                           | Dose/Frequency                                                                                                                                                                                                               | Mode of Administration                      | Self-care/Caregiver Required                   |
|-------------------------------------|--------------------------------------------------------------------------------------------------------------------------------------------------------------------------|------------------------------------------------------------------------------------------------------------------------------------------------------------------------------------------------------------------------------|---------------------------------------------|------------------------------------------------|

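### Healthcare utilisation is defined as fewer visits and admissions but is to be analysed in a binary or categorical format, which does not match the endpoint and discards information in the monthly data

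*Protocol*

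**What the plan says.** The endpoint table in protocol section 3 sets the objective "Decrease healthcare utilization" and gives its endpoint as "Reduction in healthcare visits and hospital admissions". Section 9.1 (B.iii) names the tool as a "Custom questionnaire capturing healthcare visits and hospital admissions" and the collection as "Monthly via participant health diaries and healthcare records".

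Section 12.4.3 then fixes the analysis variable: "Health care utilization will be measured by tracking healthcare events (e.g., visits, hospitalizations) in a binary or categorical format". The same sentence keeps expenditure continuous. For the secondary outcomes as a group it adds: "Mixed-effect models will calculate adjusted odds ratios to determine effect sizes". It gives no categories, cut-points or time window for utilisation, and names no count or rate analysis.

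Section 6.2 says of the monthly contact sessions: "All testing, data collection, clinical management, physiotherapy, and physical activity reviews conducted during these sessions". The protocol does not say whether attending such a session counts as a healthcare visit.

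**The concern.** A reduction in visits and admissions is a statement about quantity. The data are gathered monthly and could be added up over 12 months, yet 12.4.3 converts them to yes/no or to categories and summarises the effect as an odds ratio. A participant who goes from six visits to three is unchanged on a yes/no scale.

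Two things are at stake. The first is power: if visits are frequent, a yes/no variable over a long window can miss a real fall. The second is interpretation: an odds ratio for any visit does not answer the stated question of how much use fell. Utilisation also appears in the hypotheses (12.1) and is a named focus of the subgroup analyses (12.4.8), where precision is already lower.

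The undefined status of the monthly sessions adds to the problem. If they are counted, they enter the visit variable as contacts that the study itself arranged.

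**Working it through.** The protocol gives no visit rate, admission rate or expected effect on utilisation, so there is no figure of its own to reproduce. All rates below are assumptions, shown as a range. The two-sided 0.05 level and 90% power are taken from section 12.2, which states them for the primary outcome. Clustering is ignored throughout, so only the comparison between formats matters, not the absolute sample sizes.

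**Step 1. Chance of any visit in 12 months, Poisson counts, assumed 30% reduction.** P(any) = 1 − exp(−λ).

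- λ = 4 against 2.8: 98.2% against 93.9%.
- λ = 6 against 4.2: 99.8% against 98.5%.

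**Step 2. Information about the log rate kept by yes/no, relative to the count.**

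- Poisson: the count carries λ and the indicator carries λ²/(exp(λ) − 1), so the share kept is λ/(exp(λ) − 1). At 4: 4/53.6 = 7.5%. At 6: 6/402.4 = 1.5%.
- Negative binomial with dispersion 1: the count carries μ/(1 + μ) and the indicator μ/(1 + μ)², so the share kept is 1/(1 + μ). At 4: 1/5 = 20%. At 6: 1/7 = 14%. Here P(any) is 80% at 4 a year and 86% at 6, which is not saturated.

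**Step 3. The same Poisson formula with monthly indicators.**

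- 4 a year: λ = 0.333 a month, share kept 84%. P(any in a month) is 28%, against 21% after a 30% fall.
- 6 a year: λ = 0.5 a month, share kept 77%.

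**Step 4. Sample size per arm for an assumed 25% reduction.**

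- Yes/no: pooled-variance formula for two proportions.
- Four ordered categories (0, 1–2, 3–5, 6 or more): rank-test formula with ties.
- Count: n = (1.960 + 1.282)² × [(1/μ₁ + δ) + (1/μ₂ + δ)] / (ln 0.75)², where δ = 0 for Poisson and 1 for dispersion 1. For example, at 4 a year under Poisson: 10.507 × (0.250 + 0.333)/0.0828 = 74.1, so 75.

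| Events per year | Counts | Yes/no | Four categories | Count |
|---|---|---|---|---|
| 0.3 | Poisson | 1118 | 1109 | 988 |
| 0.3 | Dispersion 1 | 1555 | 1507 | 1242 |
| 2 | Poisson | 399 | 183 | 149 |
| 2 | Dispersion 1 | 1096 | 560 | 403 |
| 4 | Poisson | 696 | 94 | 75 |
| 4 | Dispersion 1 | 1464 | 487 | 328 |
| 6 | Poisson | 1902 | 69 | 50 |
| 6 | Dispersion 1 | 1881 | 507 | 304 |
| 12 | Dispersion 1 | 3180 | 677 | 279 |

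**Step 5. Ratios to the count analysis.**

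- Yes/no, dispersion 1: 1464/328 = 4.5 at 4 a year, rising to 3180/279 = 11.4 at 12.
- Yes/no, Poisson: 696/75 = 9.3 at 4 a year and 1902/50 = 38 at 6.
- Four categories, Poisson: 94/75 = 1.25 at 4 a year and 69/50 = 1.38 at 6.
- Four categories, dispersion 1: 487/328 = 1.5 at 4 a year and 677/279 = 2.4 at 12.
- Rare events such as admissions, at 0.15 to 0.3 a year: yes/no needs 2092/1975 = 1.06 (Poisson, 0.15) to 1555/1242 = 1.25 (dispersion 1, 0.3) times the count sample.

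**The case against.** The strongest reply is that 12.4.3 allows a categorical format as well as a binary one. Ordered categories can show a reduction at modest cost, and monthly indicators in a mixed model would keep most of the information under Poisson. The 12-month yes/no variable is one permitted reading, not a stated choice. For admissions, a binary variable costs little. Cut-points, the window and the list of countable contacts are commonly left to a statistical analysis plan. All of this stands, and it limits the size of the point.

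It does not remove the point. The protocol states the format and the effect measure, so this is a fixed choice and not a detail left open. The promise of tests suited to each variable type does not help, because the type has just been set as binary or categorical.

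A reader might infer three stronger claims, none of which the protocol supports:

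- **That the format cannot show a reduction.** Ordered categories can.
- **That visits are near saturation in this population.** The inclusion criterion ("Patients with multimorbidity, defined by two or more chronic health conditions") makes frequent visits plausible, but no visit rate is given, and with dispersion 1 even the 12-month yes/no variable is not saturated at 4 to 6 visits a year.
- **That the odds ratio would reverse because intervention participants attend monthly sessions.** This needs the sessions to be counted as utilisation and to occur in one arm only. The protocol states neither, and sections 9.2 and 10.4 describe monthly contact sessions without limiting them to one arm.

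**Conclusion.** The mismatch is real and rests on the protocol's own text: the endpoint is a quantity, the data permit counts, and the analysis is set as binary or categorical with odds ratios. A count model on the same data is better matched and never less informative in the cases examined.

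The size of the loss is conditional. It is severe only for a yes/no visit variable over a long window with frequent visits, where 7% or 1.5% (Poisson) to 20% or 14% (dispersion 1) of the information is kept at 4 or 6 visits a year. It is moderate for ordered categories and small for rare admissions. These figures assume the event rates, the form of the count distribution and a 12-month window. They also ignore clustering.

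This is a secondary endpoint, so the primary conclusion is unaffected. The change is nevertheless cheap and worth making.

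**What to change.** In section 12.4.3, replace the binary or categorical format with two separate endpoints, both over 12 months: the number of hospital admissions and the number of healthcare visits. Analyse each with a mixed negative-binomial or Poisson model that has a PHC random effect and follow-up time as offset, and report the rate ratio with its confidence interval. Keep any admission (yes/no) as a supplementary measure with an odds ratio.

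State in sections 9.1 and 12.4.3 that protocol-scheduled contact and assessment sessions are excluded from the visit count in both arms.

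The cost is a wording change and a change of model, using data that section 9.1 already collects. The one practical burden is that the utilisation questionnaire must flag study-scheduled visits. That flag is best added early, because visits already recorded without it would have to be classified afterwards.

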### 8.3 PROCEDURES FOR DISCONTINUATION/WITHDRAWAL

- **Documentation:** All discontinuations or withdrawals will be documented, including the reason and date.
- **Data Management:** Data collected up to the point of withdrawal will be retained and used in analyses unless the participant requests otherwise.
- **Continuous Communication:** Study staff will maintain regular communication to address concerns and potentially prevent withdrawal.

The principles of respect, safety, and voluntary participation will guide all decisions related to discontinuation and withdrawal. Participants will receive appropriate counselling and support throughout this process.

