## 12.2 SAMPLE SIZE DETERMINATION

- **Assumptions:**

- Mean Quality of life utility scores of control group = 0.87 [SD=0.17] (Jyani et al., 2023)
- Effect size: Based on anticipated (clinically meaningful) improvement of 10% in HRQoL scores ([name] et al., 2025)
- Power: 90%
- Significance level: 0.05
- Intra-cluster correlation: 0.24 ([name] et al., 2023)
- Attrition rate: 25%

- **Calculation Methodology:** The following steps were used for the calculation of sample size

1. Effect size calculation

Effect size is the standardized mean difference between the control and intervention groups: calculated using the following formula,

$$Effect\ Size\ (Cohen's\ d) = \frac{Mean\ difference\ (Improvement)}{SD}$$

2. Sample size for two sample t-tests

The formula to calculate the sample size for a two-sample t-test is based on the following

$$n = \frac{(Z_{1-\alpha/2} + Z_{1-\beta})^2}{d^2} * \frac{2(SD)^2}{Effect\ size}$$

Where:

- $Z_{1-\alpha/2}$  is the critical value for a two-tailed test at the significance level  $\alpha$ .
- $Z_{1-\beta}$  is the critical value corresponding to the desired power  $(1-\beta)$ .
- $d$  is the effect size.
- $SD$  is the standard deviation

The `pwr.t.test()` function in R is used to perform this calculation, which outputs the required sample size for each arm of the trial assuming a simple t-test.

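### Cost and healthcare-use endpoints ignore time observed, so unequal exit between arms would bias both comparisons

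*Protocol*

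**What the plan says.** The table in protocol section 3 gives the two economic endpoints as "Reduction in total healthcare costs" and "Reduction in healthcare visits and hospital admissions". Neither has an accrual window or a time base.

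Section 12.4.3 sets the form of each variable. For cost, "health care expenditure will be recorded as a continuous variable, capturing both mean and median expenditures". Utilisation is measured by "tracking healthcare events (e.g., visits, hospitalizations) in a binary or categorical format". The effect measure for the secondary outcomes follows: "Mixed-effect models will calculate adjusted odds ratios to determine effect sizes".

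Three other sections decide whose data enter:
- Section 8.3: "Data collected up to the point of withdrawal will be retained and used in analyses unless the participant requests otherwise".
- Section 12.3: the intention-to-treat analysis covers all randomised participants, including those who withdraw.
- Section 12.2: the assumptions list "Attrition rate: 25" per cent.

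The collection schedule is stated in two ways. Section 9.1 B describes expenditure as "Monthly data collection from participant reports and receipt submissions" and has utilisation collected monthly too. The schedule of activities in section 1.3 shows utilisation and expenditure only at 0, 6 and 12 months.

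**The concern.** Cost and healthcare use build up over time, and for both a lower value counts as better. Someone observed for three months has had a quarter of a completer's time in which to spend money or be admitted. If that partial record enters an all-randomised comparison of means, medians or any-event odds, part of the result reflects how long people were observed and not how they were cared for.

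Differential exit is plausible here. Only one arm receives the package, section 2.3.1 lists adverse events and perceived ineffectiveness as reasons for leaving, and all-cause mortality is itself an endpoint that the package is meant to change. The arm that loses more people could then show a saving that is not real, or a real saving could be hidden.

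**Working it through.** The protocol gives no cost or utilisation figure and no projected effect on either endpoint, so there is no plan figure to reproduce. The only input from the document is 25% attrition (section 12.2) over 12 months of follow-up (section 4.4). Everything else below is an assumption made to show size: exits spread evenly over the year, constant monthly cost, the same true cost and event rate in both arms, and a 30% against 20% split, which averages 25%.

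**Cost.** A participant who exits is observed for half the year on average. With exit proportion a, the observed share of the 12-month total is 1 − a/2.

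| Exit, intervention / control | Observed share | Cost ratio |
|---|---|---|
| 25% / 25% | 0.875 / 0.875 | 1.00 |
| 30% / 20% | 0.85 / 0.90 | 0.944 (false 5.6% saving) |
| 20% / 30% | 0.90 / 0.85 | 1.059 (false 5.9% excess) |

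Equal exit makes each arm's mean 12.5% too low but does not bias the ratio.

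**Utilisation as any event.** With a constant event rate r per year, a completer has an event with probability 1 − exp(−r). A participant who exits has one with average probability 1 − (1 − exp(−r))/r. The arm's probability is (1 − a) times the first plus a times the second. At 30% against 20% exit:

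| Assumed r | Intervention | Control | Odds ratio |
|---|---|---|---|
| 0.2 | 0.155 | 0.164 | 0.94 |
| 0.4 | 0.284 | 0.299 | 0.93 |
| 0.8 | 0.479 | 0.503 | 0.91 |

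The true odds ratio is 1.00 in every row, so the binary format does not escape the problem.

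**Deaths.** Suppose the arms differ only in the proportion who die, and each death carries extra cost before it, equal to k years of ordinary spending. The observed share gains d × k and loses d/2, where d is the proportion who die. The difference between arms is therefore (d in intervention − d in control) × (k − 1/2). Excess deaths look like a saving if k is below one half (six months of ordinary spending) and like an excess if k is above it. The protocol gives no figure for k, so the sign is open.

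**With time observed in the model.** Under constant monthly cost, dividing by months observed gives a ratio of 1.00 for any split of exits.

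**The case against.** A reader might infer that the protocol scores a death or early exit as a reduction, or freezes the total at exit and treats it as complete. No section says so. Section 8.3 says only that data up to withdrawal are kept and used, and the expenditure sentence in section 12.4.3 gives a variable type and two summaries. Utilisation is not a running total either, since it is binary or categorical. The claim that excess deaths would look like success also goes too far, because cost before death can cancel or reverse the effect.

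The plan can also be read differently. Section 1.3 places these measures at 0, 6 and 12 months, so they could be repeated measures in which someone who leaves has a missing value, not a low one. Section 12.4.1 mentions mixed-effects models, which could be fitted to monthly or visit-level cost without forming a truncated sum. Offsets, censoring and rules for death commonly sit in a statistical analysis plan, which is not to hand.

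These points narrow the concern but do not remove it. The total as endpoint, the binary or categorical format, the odds ratio as effect measure, and the use of partial data in an all-randomised analysis are all written in the protocol. A later plan that analysed rates would have to depart from section 12.4.3. The two readings of the schedule are themselves a reason to define the time base. The size of the effect stays hypothetical, since the split, the exit pattern and the constant cost are not in the documents.

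**Conclusion.** The concern holds in a limited form. As written, neither measure accounts for time observed, so shorter follow-up lowers total cost and the chance of any event, and exit that differs by arm biases both comparisons. Under the assumed 30% against 20% split, the false effect is about 6% on cost in either direction, and an any-event odds ratio of about 0.91 to 0.94. With equal exit there is no bias in the cost ratio. For deaths the direction cannot be stated.

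These are secondary endpoints and the primary analysis is not touched. It is still worth correcting before analysis, because the two economic objectives depend on it.

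**What to change.** In section 12.4.3:
- Replace the binary odds ratio for visits and admissions with event rates, from a mixed count model with the log of person-months to death, exit or month 12 as offset and a random effect for the health centre.
- Analyse expenditure per person-month observed with a log-link mixed model and the same random effect, reporting a cost ratio or mean difference. An odds ratio does not suit a continuous cost.
- Name this as the single main estimand for both endpoints, and report it beside the mortality result, since a rate while under observation does not show who died.

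Reconcile section 1.3 (0, 6 and 12 months) with section 9.1 B (monthly) on how these data are collected, because the person-month denominator depends on it.

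The cost is wording and programming. Section 9.1 B already specifies monthly collection and continuous monitoring of deaths, section 8.3 has the date and reason of withdrawal documented, and the exit form listed in section 15 covers mortality, migration and withdrawal. The downside is a slightly more complex model. It also assumes that those who leave would have gone on at the rate seen in comparable participants who stayed, and the report should say so.
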